### Statistical analyses

Data will be analyzed using the latest version of the Statistical Package for the Social Sciences (SPSS Inc. Chicago, IL, USA) with a significance level of *P* < 0.05 (two-tailed). Before analysis, all outcome variables will be tested for normality by the Kolmogorov-Smirnov test and, if necessary, transformed to obtain a normal distribution. Differences in variables between the two intervention groups will be calculated using the *t*-test for continuous data and the chi-squared test for categorical data. The primary outcome is the severity of posttraumatic stress levels rated by the CAPS interview at the three-month follow-up. Secondary outcomes are measures of psychosocial functioning and cardiometabolic biomarkers at three months follow-up (primary analysis). Key secondary outcomes are quality of life, plasma levels of C-reactive protein, D-dimer, cortisol and norepinephrine, as well as high-frequency heart rate variability. These outcomes are important indicators of mental health functioning, low-grade inflammation and coagulation activity as well as hypothalamic-pituitary adrenal axis and autonomic nervous system function. Repeated measures analysis of variance will be applied to test for a change in posttraumatic stress levels and in measures of psychosocial functioning and cardiometabolic biomarkers between the two follow-up visits (secondary analysis). The relative risk for developing a diagnosis of PTSD during follow-up in the control group compared to the *verum* group will be calculated by means of logistic regression analysis. For a complementary sensitivity analysis, we will apply univariate, multivariate and repeated measures analysis of covariance taking into account sociodemographic, medical and psychosocial covariates, and received psychotherapy during follow-up.

Missing values for questionnaire items will be replaced using the expectation maximization algorithm [80]. If patients drop out during follow-up, we will carry forward the last observed data points to impute missing endpoints. Randomized patients who will not undergo the intervention are excluded from the analysis. However, we will perform an additional analysis based on the intention-to-treat principle with all randomized patients.

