### Ethical considerations

The study complies with the declaration of Helsinki. The ethics committee of the State of Bern, Switzerland, approved the study protocol. All potentially eligible patients (that is, those meeting the inclusion criteria) receive written information about the aim of the study, benefits and risks of participation and the exact study procedure before giving their written informed consent to participate in the study that includes two follow-up assessments. All participants are informed that they can withdraw themselves from the study anytime. All patients are encouraged to first contact their primary care physician in case they feel a need for mental health treatment at any time during follow-up. However, these patients will remain in the study, as it would be highly unethical to ask them to refrain from seeking professional help during follow-up. Patients who are diagnosed with syndromal PTSD at follow-up investigations are told their diagnosis. Moreover, patients and their primary care physicians are informed about the possibility of a referral to the Department of Clinical Psychology and Psychotherapy, University of Bern, Switzerland to receive treatment for PTSD.

To identify adverse reactions to the *verum* intervention, two interim safety analyses will be performed after subgroups of 130 and 260 patients on the primary efficacy endpoint, that is, interviewer-rated posttraumatic stress level at three months after the intervention. The spending function approximating O’Brien-Fleming boundaries [79] will be used to determine criteria for the interim and final analyses to protect the overall false positive rate of the trial at *P* = 0.05. The study will be stopped for inequality in outcome between the *verum* and control group if results reach a predefined level of statistical significance at the two-sided alpha level of 0.001 and 0.014, respectively. The nominal two-sided significance level for the final evaluation will be 0.045. This provides us with a 3.3% and 44.2% chance of stopping the trial after the first or second interim analysis, respectively.

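### The statistical section tests at P < 0.05 without excepting the final primary comparison, for which the interim plan reserves 0.045

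*Protocol article*

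**What the plan says.** Two sections of the protocol article give a threshold that bears on the final primary test.

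- **Statistical analyses.** Data are to be analysed "with a significance level of *P* < 0.05 (two-tailed". The paragraph goes on to the t-test for continuous variables and to CAPS severity at three months as the primary outcome. It makes no exception for that outcome and does not mention the interim looks.
- **Ethical considerations.** Here, "two interim safety analyses will be performed after subgroups of 130 and 260 patients on the primary efficacy endpoint". The boundaries are of O'Brien-Fleming type and are meant "to protect the overall false positive rate of the trial at *P* = 0.05". The trial stops for a difference between groups "at the two-sided alpha level of 0.001 and 0.014, respectively". Then: "The nominal two-sided significance level for the final evaluation will be 0.045". The section adds: "This provides us with a 3.3% and 44.2% chance of stopping the trial after the first or second interim analysis, respectively".

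The Sample size calculation section uses alpha 0.05, beta 20% and a difference of 2.9 with SD 10.1, and arrives at 194 per group. This is raised by 10% to 213 per group, 426 in all.

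**The concern.** The final level of 0.045 is the price of the two earlier looks at the same endpoint. Testing the final comparison at 0.05 leaves that price unpaid, and the promised 5% overall rate no longer holds.

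An analyst working from the statistical section would find only 0.05, because the 0.045 appears once, under a heading about ethics. If the final CAPS comparison gave a P between 0.045 and 0.05, one section would call the trial positive and the other would not. The choice would then be made after the result was known.

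**Working it through.** **Inputs.** Looks at 130 and 260 patients and nominal two-sided levels 0.001, 0.014 and 0.045 (Ethical considerations); competing final level 0.05 (Statistical analyses); difference 2.9, SD 10.1, 194 per group, hence 388 evaluable (Sample size calculation). The planning effect is on the self-rated PDS, as the protocol itself says. It is used here only for power and stopping chances; the type I error does not depend on it.

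**Method.** The sequence of test statistics is treated as Brownian motion observed at information fractions 130/388 = 0.335, 260/388 = 0.670 and 1. The chance of first crossing at each look is found by numerical integration. The overall type I error is the sum over the three looks with no true effect.

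**Step 1: reproduce the interim plan.**

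- The exact O'Brien-Fleming nominal levels for three equally spaced looks at overall 0.05 are 0.00052, 0.0141 and 0.0451. The printed levels are these, rounded to three decimals.
- With 0.001 / 0.014 / 0.045 the first-crossing chances under no effect are 0.0010, 0.0135 and 0.0356. They sum to 0.0500, so the promised rate is reproduced.
- The drift at the planned effect is 2.9 / (10.1 × √(2/194)) = 2.83. Overall power is then 80.0%.
- A single test at 0.05 would need 191 to 192 per group. The stated 194 therefore fits the sequential design ending at 0.045.

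**Step 2: replace the final level by 0.05.**

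| Final level | Overall type I error, 388 analysed | Power at 194 per group |
|---|---|---|
| 0.045 | 0.0500 | 80.0% |
| 0.05 | 0.0547 | 81.2% |

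The third-look contribution rises from 0.0356 to 0.0402, and 0.0010 + 0.0135 + 0.0402 = 0.0547. With an unrounded first level of 0.0005 the total is 0.0545. The power difference is 81.2 − 80.0 = 1.2 points.

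**Step 3: sensitivity to the number analysed.** If all 426 were analysed, the looks would fall at 130/426 = 0.305 and 260/426 = 0.610. The overall error is then 0.0510 with a final 0.045 and 0.0556 with a final 0.05.

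**Step 4: the stated stopping chances.** The mean of the first-look statistic at the planned effect is 2.83 × √0.335 = 1.64.

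- First look at 0.001 (critical value 3.29): Φ(1.64 − 3.29) = 4.9%.
- First look at 0.0005 (critical value 3.48): Φ(1.64 − 3.48) = 3.3%, the stated figure.
- By the second look, cumulatively: 44.2% to 44.5%, depending on the first-look level and on whether 388 or 390 is taken as the final number. The stated 44.2% is therefore the cumulative chance. The second look alone adds 39.6% with a first level of 0.001, or 41.2% with 0.0005.

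**The case against.** The strongest reply is that a specific rule governs a general one. The 0.05 stands in an opening sentence about software and covers many secondary outcomes and models to which the stopping boundaries do not apply. The 0.045 is stated expressly for the final evaluation. Since 194 per group fits the 0.045 design, the interim plan is probably what was meant. This reading is reasonable, and it means the two sections are not strictly irreconcilable. But the document does not state it, and the default stands in the very paragraph that defines the primary test.

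A second reply is that the inflation is only about half a point. That is true, and it limits the weight of the finding. It does not remove the band from 0.045 to 0.05 in which the two sections lead to opposite conclusions.

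Three stronger readings are tempting but not supported:

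- *The sequential design itself fails to control the error rate.* It does not fail: its levels give 0.0500.
- *The error is really 0.056.* That figure combines the wrong final level with an analysis of all 426 patients. Keeping 0.045 at 426 gives 0.051. The 10% oversampling is there to cover dropouts, so a main analysis of all 426 is unlikely. The protocol also lets the spending function determine the final criterion.
- *The stopping chances are wrong.* The 3.3% follows from the unrounded first level, and 44.2% is correct as a cumulative chance. Printing 0.001 instead of 0.0005 moves the overall error by only about 0.0002.

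**Conclusion.** The point holds as a conflict of wording over one decision threshold. Applied as written, the statistical section would test the final primary comparison at 0.05 and raise the overall two-sided type I error from 0.050 to about 0.055, contrary to the stated aim of holding it at 0.05. The interim plan is sound and needs no redesign.

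The figures assume both interim looks take place at 130 and 260 analysed patients, about 388 in the final analysis, and stopping whenever a boundary is crossed. The power figures also assume the planning effect of 2.9 with SD 10.1. The mismatch in the stopping chances is an editorial matter and does not bear on this conclusion.

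**What to change.** In Statistical analyses, add that the final primary comparison (CAPS at three months) is tested at two-sided 0.045, or at the critical value given by the spending function for the actual information fractions, and that P < 0.05 applies only to the other analyses. This should be settled before the final analysis.

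As an editorial note in Ethical considerations, print the first-look level as 0.0005, which matches the stated 3.3%, and label 44.2% as the cumulative chance of stopping by the second look.

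The cost is wording only, plus about 1.2 points of power relative to a final test at 0.05. The sample size stands, since 194 per group already gives 80% power with a final level of 0.045.

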## Abstract

**Background:**

Posttraumatic Stress Disorder (PTSD) may occur in patients after exposure to a life-threatening illness. About one out of six patients develop clinically relevant levels of PTSD symptoms after acute myocardial infarction (MI). Symptoms of PTSD are associated with impaired quality of life and increase the risk of recurrent cardiovascular events. The main hypothesis of the MI-SPRINT study is that trauma-focused psychological counseling is more effective than non-trauma focused counseling in preventing posttraumatic stress after acute MI.

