## Background

Posttraumatic Stress Disorder (PTSD) is a mental disorder that may occur after the experience of a traumatic event. According to the fourth edition of the *Diagnostic and Statistical Manual of Mental Disorders* (*DSM-IV*), PTSD is characterized by three distinct clusters of symptoms consisting of 1) re-experiencing of the traumatic event (for example, in thoughts or dreams), 2) avoidance of reminders of the event and emotional numbing and 3) hyperarousal (for example, irritability and sleep problems). These symptoms must last for at least one month and cause significant problems in important areas of daily life [1]. Besides man-made and disaster-related traumatic experiences (for example, combat exposure, motor vehicle accidents, hurricanes), life-threatening illnesses, such as myocardial infarction (MI), can also cause PTSD [2-6]. A meta-analysis on clinically significant PTSD symptoms after acute coronary syndromes (ACS) found a prevalence of 16% (95% CI, 13 to 20%) [7]; two-thirds of patients continue to suffer from PTSD two years after MI [8].

Several sociodemographic and psychosocial risk factors for the risk of MI-triggered PTSD have been identified, including young age [9] and increased distress perceived during MI [10]. While MI-related threat to life, helplessness and pain are predictive of PTSD, objective markers of myocardial damage such as cardiac enzyme levels and left ventricular ejection fraction are not predictive [9,11,12]. Less than optimal care processes like emergency department crowding might contribute to MI patients’ sense of life threat and decreased control, thereby increasing the risk of developing posttraumatic stress [13].

PTSD is associated with impaired quality of life, social functioning, and high economic burden to the society [14-16]. PTSD and posttraumatic stress along a continuum of severity are predictive of incident cardiovascular disease morbidity and mortality [17-20]. A meta-analysis on three prospective studies with a total of 609 ACS patients showed that PTSD symptoms also worsen cardiovascular prognosis with a two-fold (95% CI, 1.7 to 2.4) excess risk [7]. Moreover, this relationship is maintained in studies controlling for other prognostic risk factors, including traditional cardiovascular disease (CVD) risk factors, MI severity, and depressive symptoms [21-23].

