### Sample size calculation

As opposed to the primary outcome, which is interviewer-rated posttraumatic stress, the sample size calculation is based on self-rated posttraumatic stress levels, which we had previously collected from almost 300 post-MI patients [12]. Based on these data we expect that patients at a high risk to develop PTSD (compare to below for definition) will show a mean score of 15.2 ± 10.1 (range 0 to 51) on the self-rated Posttraumatic Diagnostic Scale (PDS) at three months after MI. However, we cannot exclude a non-specific beneficial effect of the control intervention on PTSD symptom development. Therefore, we assume that patients in the control group will decrease their posttraumatic stress level by 1.0 PDS score point to 14.2 score points. We defined a 20% decrease in the posttraumatic stress level in the *verum* group compared to the control group to be clinically meaningful. Therefore, in order to achieve a 20% difference in posttraumatic stress levels between the *verum* intervention and the control group, the *verum* intervention should achieve a reduction of 3.9 PDS score points from 15.2 to 11.3 to show a clinically meaningful effect. Applying an alpha error level of *P* = 0.05, a beta error level of 20% and a group difference in the total PDS score of 2.9 ± 10.1, the sample size to detect a significant difference of 20% in posttraumatic stress levels between groups is n = 194 per group. Because of possible drop outs (including post-MI mortality), we will oversample each group by 10% (that is, n = 213 per group), yielding a total sample of n = 426 eligible post-MI patients to be randomly allocated to the two active intervention arms.

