### Study sample

Based on the recruitment experience from previous studies on PTSD in post-MI patients and other trials of the study CCU, we predict to consecutively enroll the required number of 426 eligible patients for the study within 24 months (between 1 January 2013 and 31 December 2014). Figure 1 details the recruitment and participant flow. In brief, patients with ST-segment elevation MI (STEMI) and non-STEMI and referred to the CCU, Department of Cardiology, Inselspital, Bern University Hospital, Switzerland, are invited to participate in the study. The department’s cardiologists make a diagnosis of STEMI or non-STEMI per standard criteria as previously described [38]. The average biennial admission rate of patients with STEMI and non-STEMI to the CCU is approximately 3,000. Following a secondary analysis of a previous data set [12], about 900 (approximately 30%) of these will be 'high risk patients’ in terms of perceiving a substantial amount of distress during MI (compare to. paragraph below for precise definition). Of these, we predict that one third will not be accessible, mainly because they are transferred to other hospitals early after coronary interventions or will not provide consent, leaving 600 patients meeting inclusion criteria. One fourth of these will not be eligible because they meet exclusion criteria or drop out early.

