### Measures

Table 2 shows all health outcomes in the MI-SPRINT study with the timing of their assessment. All psychometric questionnaires used in the MI-SPRINT study are validated in the German language [48-77]. We will apply the Clinician-Administered PTSD Scale (CAPS) to assess our primary outcome (that is, interviewer-rated posttraumatic stress level at three months after the intervention) [48]. Assessors will be blinded to the type of intervention and asked to indicate their guess as to whether the patient had received the *verum* intervention or the control intervention. The German version of the CAPS shows good internal consistency for the severity score of all 17 PTSD symptom items (Cronbach’s α = 0*.*88 to 0.92) as defined by the *DSMcpIV*[49]. The frequency and intensity of each symptom are rated between 0 (never) and 4 (almost always). A symptom is given when frequency is at least one point and intensity is at least two points. One of five symptoms is required for criterion B (reexperiencing cluster), three of seven symptoms for criterion C (avoidance cluster), and two of five symptoms for criterion D (hyperarousal cluster). The severity of PTSD is obtained by adding up symptom scores of criteria B+C+D. Patients will be diagnosed with syndromal PTSD if meeting criteria B+C+D [1].

**Table 2 T2:** Measures at hospital referral (T0), three-month (T1) and twelve-month (T2) follow-up

**Variables**	**T0**	**T1**	**T2**
Sociodemographic and medical variables			
Demographics: for example, gender age, marital status	x		
Medical history: for example, family history of coronary artery disease, diabetes mellitus, hypertension	x		
Lifestyle and health behavior: smoking history, alcohol consumption, physical exercise, sleep quality	x	x	x
Prescribed medication before CCU referral	x		
Medication administered during CCU stay	x		
Medication at discharge from CCU	x		
Context of hospital referral: for example, patient agitation state at arrival on CCU, hectic conditions on CCU at patient arrival	x		
Clinical presentation at time of arrival at CCU: for example, total number of stents implanted, number of diseased coronary vessels, left ventricular function, Killip classification, pain onset	x		
Psychometric data			
Clinician-administered PTSD Scale (CAPS) [48,49]		x	x
Posttraumatic Diagnostic Scale (PDS) [50,51]	x	x	x
PTSD screening with three items from the structured clinical interview for DSM-PTSD [52,53]	x		
Acute Stress Disorder Scale (ASDS) [54,55]	x		

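### The plan names a relative risk of PTSD diagnosis but obtains it by logistic regression, which yields an odds ratio; the gap depends on a control risk that the article does not give

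*Protocol article*

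**What the plan says.** Under Statistical analyses, the protocol article sets out one effect measure for the binary outcome: "The relative risk for developing a diagnosis of PTSD during follow-up in the control group compared to the *verum* group will be calculated" and then, as the method, "by means of logistic regression analysis". It mentions no odds ratio, no predicted risks, no conversion and no rare-outcome argument. It names no covariates for this model; covariates appear only in the separate analysis-of-covariance sensitivity analysis.

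The binary outcome is defined under Measures: "Patients will be diagnosed with syndromal PTSD if meeting criteria B+C+D". Table 2 schedules the CAPS interview at three and at twelve months.

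The only PTSD frequency after MI or ACS in the article is the meta-analytic 16% (95% CI 13 to 20%) in the Background, repeated in the Abstract as about one in six. It concerns clinically significant symptoms after acute coronary syndromes in general. The trial itself enrols only patients screened as high risk; under Study sample, "about 900 (approximately 30%) of these will be 'high risk patients". The article states no expected risk of the diagnosis in either arm.

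The planning effect is set on the continuous score, not on the diagnosis: "We defined a 20% decrease in the posttraumatic stress level in the *verum* group compared to the control group to be clinically meaningful".

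**The concern.** The sentence names both the quantity to be reported and the model that is to produce it, and the two do not match. A reader who sees a figure labelled as a relative risk will read it as a ratio of probabilities. If the figure is in fact the exponentiated logistic coefficient, it is a ratio of odds. With control over verum and a benefit of verum, that ratio is always the larger of the two, so the mislabelling would favour the intervention.

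This is the only effect measure that the article names for occurrence of the diagnosis. It is the figure that a later reader or meta-analyst would take as the preventive effect on PTSD. Since both estimand and method are stated, this is not a detail left to a fuller document.

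**Working it through.** **Figures in the plan.** The article gives no incidence, relative risk, odds ratio or power for the PTSD diagnosis, so there is no figure of its own to reproduce on this point. Its sample size (194 per group) concerns the mean self-rated score. With a difference of 2.9, SD 10.1, two-sided alpha 0.05 and 80% power, I obtain 191 per group by the normal formula and 192 by the t-test, within 3% of the stated figure. That calculation does not depend on the binary outcome.

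**Inputs.** Let pc be the risk of diagnosis in the control group and pv the risk in the verum group. Neither is in the article. I take pc from 5% to 30% as an assumption. The 16% within that range is borrowed from the symptom-level figure in the Background. The 30% is an assumed risk and has no connection with the share of admissions expected to be high risk. True relative risks of 1.25 and 2.0 are illustrations only.

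**Formulas.**

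- Relative risk: RR = pc / pv
- Odds ratio: OR = [pc/(1 − pc)] / [pv/(1 − pv)]
- OR − 1 = (pc − pv) / [pv(1 − pc)] and RR − 1 = (pc − pv) / pv
- Hence (OR − 1)/(RR − 1) = 1/(1 − pc)

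On the control-over-verum scale, the inflation of the excess over 1 therefore depends on the control risk alone, whatever the true effect.

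**Worked example.** With pc = 0.16 and pv = 0.08, RR = 2.00. The odds are 0.16/0.84 = 0.1905 and 0.08/0.92 = 0.0870, so OR = 2.19. The excess is 1.19 instead of 1.00, and 1/(1 − 0.16) = 1.19.

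**Range.**

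| Assumed control risk | OR when RR = 1.25 | OR when RR = 2.0 | Ratio too high by (RR 1.25 / 2.0) | Excess over 1 too high by |
|---|---|---|---|---|
| 5% | 1.26 | 2.05 | 1% / 3% | 5% |
| 10% | 1.28 | 2.11 | 2% / 6% | 11% |
| 16% | 1.30 | 2.19 | 4% / 10% | 19% |
| 20% | 1.31 | 2.25 | 5% / 13% | 25% |
| 30% | 1.36 | 2.43 | 9% / 21% | 43% |

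**Model check.** I fitted both models to the same two-by-two tables (1,000 per arm). For 16% vs 12.8%, 16% vs 8%, 30% vs 24% and 30% vs 15%, the logistic model returned 1.298, 2.190, 1.357 and 2.429. The log-link Poisson model returned 1.25, 2.00, 1.25 and 2.00.

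**Other scale.** Inverted to verum over control, the apparent reduction is inflated by 1/(1 − pv). With the same illustrations at 16% and 30%, the factors are 1/0.92 = 1.09, 1/0.872 = 1.15, 1/0.85 = 1.18 and 1/0.76 = 1.32, that is 9% to 32%. For example, at a control risk of 16% a true 20% reduction reads as 23% (OR 0.77).

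**The case against.** The best reply is that this is loose wording with little consequence. A relative risk can be derived from a logistic model through its predicted risks, and the article does not say that the raw exponentiated coefficient will be reported. Misreporting is therefore possible but not shown. If treatment group is the only term in the model, the relative risk can also be read straight from the two-by-two table. This stands as far as it goes, but no such step is stated, and the sentence as written leads to the odds ratio.

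A second reply concerns size, and it is right. A reader might infer that the outcome is common and the inflation therefore large. The article does not establish this. Its 16% counts clinically significant symptoms in general patients after an acute coronary syndrome, whereas the outcome here requires all three symptom clusters on the interview and may be rarer. Restriction to high-risk patients, and two interviews over which cases can accumulate, push the other way. The net risk is unknown, so a fair range must include low values, where the discrepancy is negligible.

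A reader might also take the word incidence in the title to make this analysis central. The title speaks of posttraumatic stress, and the primary outcome under that name is the continuous CAPS severity score, not the diagnosis. Nor is the control-over-verum direction an error: it is stated openly, and its reciprocal carries the same information.

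**Conclusion.** The mismatch between measure and method is on the face of the text and holds at any incidence. Its size cannot be fixed from the article. On the planned scale, the excess over 1 is overstated by about 5% if the control risk is 5%, rising to 43% if it is 30%. The ratio itself is off by 1% to 21% over that range for true relative risks of 1.25 and 2.0. These figures rest on assumed control risks and assume that the exponentiated coefficient is what would be reported. A claim of serious inflation would need a control risk of about 20 to 30% or a large effect, and the article supports neither.

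The point is minor. The diagnosis is neither the primary outcome nor among the listed key secondary outcomes. The sample size does not rest on it, and the chi-squared comparison of the groups is unaffected. It is still worth correcting, because the error would favour the intervention and costs almost nothing to remove.

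**What to change.** Replace the sentence with one whose method matches its measure. Either:

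- estimate the relative risk with a log-binomial model, with Poisson regression and robust variance, or by standardising logistic predictions (directly from the two-by-two table if the analysis is unadjusted), and report the risk in each arm and the risk difference with confidence intervals; or
- keep the logistic model as it is and call the result an odds ratio, preferably with the risk in each arm beside it.

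The cost is one sentence. No new data are needed, and the log-binomial and Poisson models can be fitted with the generalized linear models procedure of SPSS, the package already planned.
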